### Intervention: S-FAME

S-FAME is an adaptation of the FAME model for a municipal social services context [18]. To avoid conceptual confusion with the earlier clinical feasibility pilot, the intervention should be understood as an adapted implementation package rather than only as a list of therapeutic components. The shared core is family-centered work with digital media-related routines, conflict reduction, and parent-child communication. The social services adaptation concerns how families enter the program, who delivers it, how risk and safeguarding issues are handled, how the program is presented as early support, and how the model fits ordinary municipal resources.

The program is delivered by trained social services staff or other qualified municipal personnel using a manual, facilitator training, session materials, and fidelity-support procedures. Content may include psychoeducation about digital media and health, structured family discussions about expectations and boundaries, exercises that help families identify conflict triggers, strategies for emotion regulation and de-escalation, and routines that protect sleep, school attendance, and offline activities. The emphasis in this protocol is not that these components are novel in themselves, but that they are packaged, delivered, and evaluated within a new preventive service setting.

For a detailed description of the program theory and logic model, please see Werner, Kapetanovic, and Claesdotter-Knutsson [18].

### Outcomes and measures

Assessments will be completed at baseline before randomization, immediately after the intervention period, and 1 month after program completion.

Child-reported measures will include the Gaming and Social Media Questionnaire (GSMQ-9) [22], Kessler Psychological Distress Scale-6 (K6) [23], Parenting Children and Adolescents (PARCA) items [24], Family Check-Up (FCU) warmth and conflict items [25], the Insomnia Severity Index for Adolescents (ISI-A) [26] or the version specified by the research team, and background information including age, gender, height, weight, living situation, and prior or current [EC5] child mental health service contact.

Parent-reported measures will include parent version of GSMQ-9, PARCA, FCU warmth and conflict items, and any additional service use, cost, work absence, or family resource measures required for the health economic evaluation.

### Qualitative and implementation evaluation

The qualitative component will examine more than satisfaction with the program. It will investigate how families understand the offer of support from social services, whether S-FAME feels accessible and non-stigmatizing, how children and parents experience joint participation, and which parts of the program are most useful or difficult to apply at home. Approximately 15 to 20 children and 15 to 20 parents will be interviewed by trained research assistants [27] within one month after participation, with final sample size guided by information power and thematic saturation.

Focus groups with social workers and group leaders will examine implementation fit, training needs, fidelity, perceived appropriateness for the target group, burden on ordinary services, safeguarding boundaries, and the feasibility of offering S-FAME without a prior individual needs assessment when legally and locally appropriate. Notably, it is necessary to understand whether the model can become part of routine municipal preventive work.

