**Methods:**

Families with children aged 10–14 years who seek municipal social services support because of digital media use (including gaming and excessive social media use) or related family conflict will be recruited from participating municipalities. Atleast176 families will be randomized in a 1:1 ratio to immediate S-FAME or a condition consisting of regular support from social services during the study period and subsequent access to P-FAME, a three-session online intervention for parents. S-FAME is delivered by trained municipal staff and retains selected family-centered principles from FAME while adapting content, referral pathways, risk management, and implementation procedures to preventive social services. Quantitative outcomes will be collected at baseline, postintervention, and 1-month follow-up. Qualitative interviews and focus groups will explore family and staff experiences, implementation fit, and the balance between fidelity and local adaptation. A health economic evaluation will estimate implementation costs and potential cost-effectiveness from municipal and broader societal perspectives.

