## Objectives

The overarching aim is to evaluate S-FAME as an adapted, municipal social services intervention for families with children aged 10–14 years experiencing digital media-related conflict, problematic gaming, or excessive screen use.

The specific research questions are as follows:

Does S-FAME reduce child digital media-related problems compared with the comparator pathway?Does S-FAME improve parenting practices, parent–child communication, and perceived warmth and conflict in the family?Are changes in parenting behavior and family interaction associated with changes in child screen-related outcomes?Is S-FAME feasible, acceptable, and appropriate for delivery by municipal social services staff?What implementation conditions support or hinder delivery, fidelity, family engagement, and scale-up?What are the costs and potential cost-effectiveness of S-FAME from municipal and societal perspectives?What are the experiences of children and families who participate in S-FAME, and how do they understand and engage with the support offered through social services?

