### Recruitment and eligibility

Families will be recruited through participating municipal social services when parents or children seek support for repeated digital media use conflict, impaired routines, parental concern, or child functioning problems. The target group is families who experience digital media-related difficulties severe enough to seek structured support from social services. Based on power analyses appx 176 participants will be required to detect a small effect size (d = 0.03), accounting for potential attrition. Eligible families must include a child aged 10–14 years; at least one parent or legal guardian willing to participate (note: both child and parent participation is required for S-FAME delivery); reported concern related to gaming, social media use, other digital media activities, or screen-related family conflict; and sufficient Swedish language ability to participate in sessions and complete measures. Families will be excluded when acute safeguarding concerns, severe psychiatric instability, ongoing crisis, or another service need makes participation in a group-based preventive intervention inappropriate.

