### Limitations

Potential limitations include recruitment, reliance on self-report measures, short follow-up, variation in municipal implementation, and possible differences between families who seek support and those who do not. The comparator pathway may also vary across municipalities if treatment as usual is not standardized. These limitations should be addressed by transparent reporting of local procedures, monitoring of implementation fidelity and adaptations, and sensitivity analyses when feasible.

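### The interview window about S-FAME closes when the 1-month questionnaire falls due, so some S-FAME families will probably have an extra research contact before a self-reported outcome

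*Protocol article*

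**What the plan says.** Under Qualitative and implementation evaluation, the protocol article fixes both the number and the timing of the interviews: "Approximately 15 to 20 children and 15 to 20 parents will be interviewed by trained research assistants [27] within one month after participation". The same section lists what they explore, including "whether S-FAME feels accessible and non-stigmatizing, how children and parents experience joint participation", and which program elements families find helpful or hard to put into practice. The matching research question under Objectives is "What are the experiences of children and families who participate in S-FAME".

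Under Outcomes and measures, the assessments after baseline are set "immediately after the intervention period, and 1 month after program completion". They are questionnaires completed by the child and the parent, covering gaming and social media problems, parenting, and warmth and conflict in the family. The child also reports distress and sleep. The Limitations section names "reliance on self-report measures, short follow-up" among the trial's weaknesses.

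No sentence says whether an interviewed family completes its 1-month questionnaire before or after the interview.

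**The concern.** A research interview about the program is itself a contact with the family. It invites children and parents to reflect on routines, conflict and communication at home, which the 1-month questionnaires then ask the same people to rate. Such a conversation could rehearse the program content or change how a family judges its own situation.

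Controls receive usual support during the study period and are offered P-FAME only afterwards. They have no S-FAME experience to be interviewed about, so any effect of the interview enters one arm only. Families know what support they received, and the listed child and family outcomes are self-reported or parent-reported, so no objective measure stands beside them.

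At stake is the clean reading of the 1-month contrast. For part of the S-FAME arm it would compare S-FAME plus a research interview with usual support. That time point is the only one after the immediate post-intervention assessment, so it carries all of the trial's quantitative evidence on whether an effect lasts.

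**Working it through.** **Timing, side by side.** Take participation to mean taking part in S-FAME, which is how the surrounding text and the research question use it.

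- Interview window: from program end to one month after it.
- Immediate post-intervention assessment: at program end, so normally before any interview.
- 1-month questionnaire: due one month after program end, which is the point at which the interview window closes.

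An interview held on plan therefore falls before the last questionnaire, or at the latest around it. Nothing places the questionnaire first.

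**Inputs.**

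- Trial size: "Atleast176 families will be randomized in a 1:1 ratio to immediate S-FAME" (abstract, Methods). Per arm: 176 / 2 = 88 families.
- Interviewed: 15–20 children and 15–20 parents.
- Effect of one interview on a reported score: not in the documents. Assumed range 0.1–0.3 SD in those interviewed.
- All interviewees are taken to be S-FAME families interviewed before the questionnaire. This is the least favorable case.

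**Share directly exposed, for one informant.** Share = interviewed / 88.

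- 15 / 88 = 0.170, or 17%
- 20 / 88 = 0.227, or 23%

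The share is somewhat higher among retained families if interviewees are mostly retained, and lower if more than 176 families are randomized.

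**Shift in the 1-month S-FAME mean.** Shift = share × assumed interview effect.

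| Interviewed | Effect 0.1 SD | Effect 0.3 SD |
|---|---|---|
| 15 | 0.170 × 0.1 = 0.017 | 0.170 × 0.3 = 0.051 |
| 20 | 0.227 × 0.1 = 0.023 | 0.227 × 0.3 = 0.068 |

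The range is about 0.02–0.07 SD. If the interviews follow the questionnaire, the shift is 0.

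**A yardstick.** The plan's own sample-size statement is "Based on power analyses appx 176 participants will be required to detect a small effect size (d = 0.03), accounting for potential attrition". It does not reproduce. With n per arm = 2(1.960 + 0.842)² / d², two-sided 5% and 80% power (both assumed), d = 0.03 needs 17,442 per arm. That mismatch is a separate matter, so the printed d is not used here. With 88 per arm, the same formula gives d = √(2 × 7.849 / 88) = 0.42 as the difference detectable with 80% power, before attrition. A shift of 0.07 SD is 0.07 / 0.42, about one sixth of that, and 0.02 SD is about one twentieth.

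**The case against.** The strongest reply is that the article fixes no order. Within one month is an upper limit, the questionnaire has no stated visit window, and participation is not defined as program completion. An interview could share the questionnaire's contact or follow it, and a fuller protocol that is not shown may settle the sequence. This stands against any claim that interviews certainly come first. It does not remove the point, because the window as written lies almost wholly before the questionnaire's due date.

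Three stronger readings are tempting, and the documents do not support them.

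- *The interviews are restricted to one arm.* The topics and the research question strongly imply this, but no sentence says it.
- *The bias favors S-FAME.* The interviews also cover what families find hard to apply. Talking about difficulties could sharpen awareness of problems and worsen reported scores. The sign is open.
- *Up to 40 of 88 families, 45%, are exposed, and the mean moves by 40 / 88 × 0.3 = 0.14 SD.* This needs 20 children and 20 parents from 40 different families, every interview before the questionnaire, and a full 0.3 SD effect on family members who were not interviewed. No passage supports that spill-over.

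Two further replies have some force. Interviewing soon after the program protects recall in children aged 10–14, which is a real but modest cost of moving the interviews. A sensitivity analysis without interviewed families would keep early interviews. It is the weaker remedy, because interviewees are selected after randomization, so leaving them out can itself unbalance the arms.

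**Conclusion.** The point holds as a minor design weakness. The stated interview window makes it likely that some S-FAME families have an extra reflective contact before the 1-month self-reported outcome, with no counterpart among controls. The probable size is 0.02–0.07 SD on the 1-month S-FAME mean for any one informant. This rests on 88 families per arm, 15–20 interviewees per informant type, all of them in the S-FAME arm and interviewed before the questionnaire, and an assumed interview effect of 0.1–0.3 SD that has no source in the documents. The direction is uncertain.

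The immediate post-intervention contrast should be unaffected. The article names no primary time point, so a reader should not infer that the trial's main comparison is compromised. The case for acting rests on how little the change costs, not on a large expected bias.

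**What to change.** In Qualitative and implementation evaluation, replace the current timing with a sequencing rule: each family's child and parent interviews take place only after that family has completed its 1-month questionnaire, or after the window for it has closed, and ideally directly afterwards.

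The cost is slightly longer recall in the interviews, kept to a minimum if the interview directly follows the questionnaire. No extra staff are needed. Because only 15–20 children and 15–20 parents are required, they can be drawn from families recruited earlier, so the analyses planned for the first quarter of 2027 need not move.

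If early interviews are kept for the sake of recall, record the dates of interview and questionnaire for each family. A sensitivity analysis of the 1-month outcome without families interviewed first can then be reported, with the caveat that this exclusion is made after randomization.

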### Health economic evaluation

The health economic evaluation will estimate the costs of preparing, training, delivering, supervising, and maintaining S-FAME in municipal services. If the outcome data support it, the analysis will compare costs with effects on prespecified child and family outcomes and will explore cost-effectiveness or cost-benefit from municipal and broader societal perspectives. Relevant cost categories may include facilitator time, training, materials, coordination, service use, parent work absence, and downstream support needs.

Health economic evaluations of preventive family interventions in social services typically adopt a societal perspective that extends beyond direct service costs to include productivity losses, downstream service use, and family burden [28]. In the present study, costs will be estimated using a micro-costing approach [29], capturing facilitator time, training and supervision, materials, and administrative coordination through structured cost logs and staff time records. If the primary effectiveness outcomes show a statistically or clinically meaningful between-group difference, an incremental cost-effectiveness analysis will be conducted, expressing results as cost per unit improvement on the primary child outcome measure. A cost-benefit analysis may additionally be explored if downstream service use data permit monetization of outcomes [30]. Uncertainty in cost and effect estimates will be addressed through probabilistic sensitivity analyses and presented using cost-effectiveness acceptability curves [30]. All cost data will be reported in Swedish kronor (SEK) and converted to Euro for international comparability, using the exchange rate at the time of analysis.

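### The incremental cost-effectiveness analysis depends on a favourable effectiveness result, so a stated research question may go unanswered and, when the ratio is reported, its effect is overstated on average

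*Protocol article*

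**What the plan says.** The Objectives section of the Protocol article asks without condition: "What are the costs and potential cost-effectiveness of S-FAME from municipal and societal perspectives". The abstract's Methods paragraph is equally unconditional: "A health economic evaluation will estimate implementation costs and potential cost-effectiveness from municipal and broader societal perspectives".

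The Health economic evaluation section treats the two halves of that question differently. The costing is unconditional: "The health economic evaluation will estimate the costs of preparing, training, delivering, supervising, and maintaining S-FAME in municipal services". The comparison of costs with effects is not. One sentence begins: "If the outcome data support it, the analysis will compare costs with effects on prespecified child and family outcomes". A later one sets the rule for the incremental analysis: "If the primary effectiveness outcomes show a statistically or clinically meaningful between-group difference, an incremental cost-effectiveness analysis will be conducted", with the result given by "expressing results as cost per unit improvement on the primary child outcome measure". The same section then says: "Uncertainty in cost and effect estimates will be addressed through probabilistic sensitivity analyses and presented using cost-effectiveness acceptability curves". The article provides no incremental analysis for the case where the condition is not met.

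**The concern.** Cost-effectiveness is a question about incremental cost and incremental effect taken together, with the uncertainty in both. A non-significant effect is not a zero effect and does not settle whether the programme is worth its cost. Probabilistic sensitivity analysis and acceptability curves exist to express that uncertainty, and neither needs a significance test first.

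The rule has two consequences. When the condition fails, a municipality gets S-FAME's costs but no planned estimate of cost per unit of benefit, just when uncertainty is greatest. When it is met, the ratio is computed because the observed effect was large, and that same effect is the ratio's denominator. Selecting on the denominator overstates it on average and so tends to understate cost per unit gained.

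**Working it through.** **Inputs.** The total is about 176 (Recruitment and eligibility) and allocation is 1:1 (Randomization and control group), so 176/2 = 88 per arm. The article gives no alpha, SD, size of clinically meaningful difference, baseline correlation or attrition rate. I assume two-sided 5% and SD 1, and vary the rest.

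**The plan's own figure.** The article states: "Based on power analyses appx 176 participants will be required to detect a small effect size (d = 0.03), accounting for potential attrition". At 80% power (assumed), n per arm = 2(1.960 + 0.842)²/d². For d = 0.03 this is about 17,442 per arm, so 176 does not reproduce. For d = 0.3 it is 175 per arm (a t-test calculation gives 175.4), close to 176 per arm rather than in total. That mismatch is a separate matter. Here it means only that the true d must be a range. With 88 per arm, 80% power is reached at d of about 0.42.

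**Method.** Let the estimate D be normal with mean d and SE = √(2/88) = 0.1508. The condition is met in S-FAME's favour when D exceeds a cut-off c. With a = (c − d)/SE:

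- P(run) = 1 − Φ(a)
- E[D | run] = d + SE × φ(a)/(1 − Φ(a))

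Significance only: c = 1.96 × 0.1508 = 0.2955. Looser condition, taking an estimate of at least 0.2 as clinically meaningful (assumed): c = 0.2.

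**Worked case, d = 0.3, significance only.** a = (0.2955 − 0.3)/0.1508 = −0.03, so P(run) = 0.512. E[D | run] = 0.3 + 0.1508 × 0.399/0.512 = 0.417, and 0.417/0.3 = 1.39.

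**Results, 88 per arm, no baseline adjustment.** The effect ratio is mean estimate over truth, given that the analysis is run. The ICER (cost per unit) ratio is the median over truth, with incremental cost held fixed and positive.

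| True d | Significance only: run | Effect ratio | Median ICER ratio | Looser: run | Effect ratio | Median ICER ratio |
|---|---|---|---|---|---|---|
| 0.2 | 26% | 1.93 | 0.54 | 50% | 1.60 | 0.66 |
| 0.3 | 51% | 1.39 | 0.75 | 75% | 1.22 | 0.86 |
| 0.42 | 80% | 1.13 | 0.91 | 93% | 1.05 | 0.97 |
| 0.5 | 91% | 1.05 | 0.97 | 98% | 1.02 | 0.99 |

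**Sensitivity at d = 0.3.**

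- Baseline adjustment, assumed correlation 0.5: SE = √(2 × 0.75/88) = 0.1306. Significance only: run 63%, effect ratio 1.26. Looser: 78%, 1.17.
- Assumed 20% attrition, about 70 per arm: SE = √(2/70) = 0.169. Significance only: run 43%, effect ratio 1.52. Looser: 72%, 1.26.

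**Without the condition**, the analysis is always run and the effect estimate in the denominator is not subject to this selection.

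**The case against.** Several points on the other side have force.

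- *The condition is met by significance or by clinical meaning.* Significance-only figures are therefore the harsher branch. A reader might infer from 51% that the analysis is a coin toss even if S-FAME works. The article does not support that: it prints no d of 0.3, the looser branch gives 75%, and Statistical analysis plans to account for baseline values, which raises the chance further.
- *The bias is an average.* A reader might conclude that every reported ratio would be biased towards S-FAME. That goes too far. The overstatement is a mean over repeated trials, becomes small at high power, and favours S-FAME only if incremental cost is positive. Under the looser condition at d = 0.42 and above, the mean ratio slightly exceeds the truth because ratios are skewed, although the median stays below it.
- *The phrase about outcome data supporting the comparison may concern data quality.* That reading is open, so the phrase cannot be counted as a second results-based condition. It needs clarifying.
- *A threshold for clinically meaningful may stand in an analysis plan that is not shown.* Agreed, so its absence is not held against the article.
- *Comparator costs.* A reader might infer that cost logs cover S-FAME only. The micro-costing sentence names no arm, and service use is planned in both Outcomes and measures and Health economic evaluation without restriction by arm. The inference is not established.
- *The costing is unconditional and the component is secondary.* True. The cost half of the question is answered, and randomization and the primary effectiveness estimate are untouched.

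None of this removes the condition. The acceptability curves do not rescue it either, since a curve for cost per unit of effect exists only if the incremental analysis is run.

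**Conclusion.** The point holds, as something that should be fixed before analysis but does not threaten the trial's main result. The article states a rule that conflicts with its own unconditional research question and abstract.

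Across true d from 0.2 to 0.5 with 88 per arm, the chance that no incremental analysis is run goes from 74% down to 9% under significance alone, and from 50% down to 2% under the looser condition. When it is run, the mean effect is overstated by 93% down to 5%, or by 60% down to 2%. Baseline adjustment reduces these figures and attrition increases them. All rest on the assumed d, alpha, SD and reading of clinically meaningful; the conflict with the stated question rests on none of them.

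**What to change.** In Health economic evaluation, delete the clause that makes the incremental analysis depend on a statistically or clinically meaningful difference. Suggested text: *The incremental cost-effectiveness analysis will include all randomized families and will be done whatever the effectiveness result. Joint uncertainty in incremental cost and effect will be shown by probabilistic sensitivity analysis and cost-effectiveness acceptability curves.*

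Reword the earlier conditional sentence so that it refers only to availability or quality of the data, not to a favourable result.

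The cost is wording, a little more analysis, and possibly having to report an uncertain ratio. No extra data collection is needed. Recruitment is planned to December 2026 and analysis for the first quarter of 2027; the change carries most weight if it is made and registered before any outcome comparison is seen.
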